**COLLABORATORS:**

1) [name], CRS Clinical Manager

2) [name], Nurse Manager, Inpatient Allogeneic BMT Units & Allogeneic Pre- Transplant

3) [name], CRS Registered Dietitian

4) [name], AlloBMT Nurse Coordinator

5) [name], CRS Kinesiologist

6) [name], AlloBMT Registered Dietitian

7) [name], UHN Biostatistician

8) [name], CRS Occupational Therapist

9) [name], AlloBMT Nurse Coordinator

10) [name], CRS Physiotherapist

11) [name], AlloBMT Registered Dietitian

**1.0 BACKGROUND:** Allogeneic blood and marrow transplantation (alloBMT) is a curative treatment for many hematologic cancers and its use has increased rapidly over the past decade. While effective, alloBMT is associated with numerous treatment-related physical and psychosocial side effects, reduced physical functioning, and worsening nutritional status which are associated with increased risk of complications (i.e. infections, drug toxicity, weight loss, graft failure & graft‐versus‐host disease), significant early and late treatment related mortality, and can profoundly affect quality of life (QoL).

As a result, ***there have been calls for increased attention to the management of adverse effects associated with alloBMT with the goal to minimize dysfunction, maximize well-being and QoL, and reduce treatment-related mortality*.**

Cancer rehabilitation is now considered an essential component of cancer care and focuses on

prevention and treatment of the adverse effects of cancer and treatment and to optimize functional status and QoL. Embedding multidimensional longitudinal (pre to post transplant) rehabilitation programs that focus on exercise, nutrition and teaching self-management skills as a standard part of treatment for individuals undergoing alloBMT has potential to mediate the significant adverse effects, improve survival, and reduce burden on the healthcare system. While patients typically receive some in-patient rehabilitation, this is a small part of the alloBMT pathway and services are quite limited. Currently, transplantation centers across North America generally do not offer longitudinal rehabilitation programs and research is urgently needed to test the acceptability and effectiveness of these programs using innovative delivery strategies that have the potential for future scalability and to

understand the associated costs. ***In response, through a strong collaboration between the PM Cancer Rehabilitation and Survivorship (CRS) and alloBMT teams, we developed an innovative multicomponent rehabilitation intervention for patients undergoing alloBMT (CaRE-4-alloBMT).***

**2.0 PROGRAM DESCRIPTION (*see Appendix 1*):** CaRE-4-alloBMT is a longitudinal 6-month rehabilitation program (peri to post transplant) adapted from an existing evidence-based and effective model developed by the CRS team (CaRE@ELLICSR and CaRE@Home). The program is informed by established behaviour change theory and harnesses current and emerging eHealth technologies to reduce barriers to accessing and providing cancer rehabilitation. CaRE-4-alloBMT uses a person- centred strategy and a multidimensional approach targeting physical activity, nutrition, psychosocial distress and promoting self-management skills. Innovative components of CaRE-4-alloBMT include:

**1) *Individualized progressive exercise prescriptions*** developed and monitored by CRS registered kinesiologists and supported with a web/mobile application (Physitrack) that allows customizable exercise prescriptions, tracking of exercise completion, and video tutorials. The initial personalized exercise program will be given to a participant following the initial assessment. A program will be created based on the specific needs and physical condition of each participant. The participant will receive the detailed exercise program via Physitrack (includes exercise description and videos of each exercise). Each exercise program will contain cardiovascular and strength training as well as stretching exercises. The exercise program will be revised and progressions will be added based on the individual’s needs after the follow-up assessments or during the scheduled check-ins between assessments. Check-ins are scheduled as follows:

- - At 2 and 4 weeks after initial assessment
  - 8 weekly check-ins following discharge
  - At 10 and 12 weeks following discharge

The participant can contact the Kinesiologist by e-mail at any point during the program.

**2) *Individualized nutrition plans and stepped stratified* care** (education, counselling, intervention) based on nutritional status and delivered by registered dietitians (alloBMT and CRS). As part of standard of care, all patients receive a nutrition assessment and their caloric intake goals are set. Those in the INT arm (CaRE-4-alloBMT plus usual care group) will receive additional nutritional education through the e-modules and monitoring of caloric intake through the Fitbit. They will also have access to meal preparation and recipes through ellicsrkitche.ca. Patients can track their nutritional intake on their Fitbit device and this data will be monitored weekly by the RKin. Patients who falls below 50% of their goals (based on intake assessment) will flagged to the RD for follow up.

**3) *On-line e-modules*** (developed in collaboration with PM Oncology Education) provide interactive education to promote self-management skills on crucial topics (i.e. stress management, nutrition, managing common symptoms). There will be 9 online e-modules:

- - Introduction: Getting started
  - Eat and Cook for Wellness
  - Exercise
  - Manage your emotions
  - Reduce Fatigue
  - Being Mindful
  - Boost your Brain Health
  - Stay Connected
  - Planning for the Future

Participants will be asked to complete all 9 modules. Each module should take between 20-30 minutes to complete. Participants can go through these modules at their own pace. Patients will receive a link for the online modules. Patients will be able to access the module by entering their e-mail address and creating their own unique password.

**4) *Remote monitoring using*** FitbitTM devices to monitor patients physical activity, caloric intake, and sleep for duration of the program. CRS and alloBMT clinicians will have access to real-time Fitbit data through our clinical dashboard (developed in collaboration with TECHNA). The Fitbit is also known to promote behaviours change and allows for self-monitoring and feedback. Participants will be asked to wear the Fitbit for the duration of the study. Participants will only need to add their meals to monitor their nutrition. No other action is required from the participants once the account has been created. This will replace the paper based food diary they must keep (standard of care). The account for the participant will be created by the RA or RKin and the participant will then be able to access the app via an email link. The RA or RKin can assist/provide support to the participant as needed to access the app. If the participant is unable to download or use the app a detailed print out of their exercise program will be provided.

The following information will be required to create an account:

- - First name
  - Last name (participant study number will be entered in this field
  - Year of birth
  - Email address

Both the participant and Kinesiology team will have access to this information but the account information is not visible to third parties. Physitrack provides links to the privacy policy and terms of use/agreement and is available for the participant to review as needed.

**5) *Remote clinical support:*** Pre/Post discharge, patients will have scheduled (PHS) remote check-ins and health coaching sessions with a member of the CRS team (phone or MS Teams video). These occur in week 2,4 (pre) and 1-8,10,12 (post-discharge).
*Frequency of check-ins and what will be discussed:* Check-ins are by telephone or MSteams video and scheduled as follows:

- - At 2 and 4 weeks after initial assessment (pre-BMT admission)
  - Weeks 1-8, 10 and 12 post-discharge (post-BMT dischange)
- Check-ins discussion using motivational interviewing techniques and focus on
  - Adherence to exercise program
  - Changes to exercise program based on participant’s needs
  - Module completion
  - Answering participants questions

The program strongly aligns with the SUNDAE framework (***see Appendix 1***).

**3.0 OBJECTIVES AND METHODS:**

**Objectives:** i) To test the feasibility and safety of CaRE-4-alloBMT plus standard best practice cancer

care compared to standard best practice cancer care alone; ii) To assess the preliminary efficacy of CaRE-4-alloBMT on *physical function*, *disability*, *nutritional status, distress, QoL, healthcare utilization, and survival* and estimate *program return on investment.*

**Methods (*see Appendix 2*):** We will conduct a Phase II feasibility RCT in patients undergoing alloBMT at Princess Margaret Cancer Centre. Patients will be randomized to receive usual care (n=40) or CaRE-4-alloBMT plus usual care (n=40). **Procedure:** Potential participants will be identified from weekly-generated clinic lists. Eligible participants will be identified by transplant nurse coordinators and oncologists during the initial pre-transplant consultation. Nurse coordinators/oncologist will introduce study to the patient. The study information letter will be added to the information package that patients receive at this appointment, if patient agrees to receive letter. The nurse coordinators/oncologist will provide the research assistant (RA) with a list of patients that agreed to be approached for this study.. The consent process will be opt in, and written informed consent will be obtained by the RA. After patients consent for transplant, the clinic staff will provide the study RA with a list of patients who have consented to transplant and have consented to be approached for study purposes. The RA will approach eligible patients at one of their usual care medical appointments to review consent form and answer any questions they may have regarding the study. If the patient agrees to participate and has no further questions, their consent will be obtained and a signed copy of the consent will be given to them. The RA will email patients a link to the REDCap questionnaire package a week prior to baseline assessment (T0); if preferred, patients can choose to complete a paper-based questionnaire at T0 instead. At baseline assessment (4-6 weeks pre-transplant), participants will undergo a 60-minute physical assessment. Following the assessment, patients will be randomized (1:1 stratified by age and clinical frailty score at pre-transplant consultation). Follow-up assessments will be conducted at: transplant hospital admission (T1), hospital discharge (T2), and 3-months post-discharge (T3). A week prior to each assessment, RA will email participants the link to the online questionnaire package. We will use REDCap, which is the preferred system for online questionnaires at UHN. If the participants prefer, they can complete a printed version of the questionnaire package on the day of the assessment instead of completing it online. Participants in the CaRE-4-alloBMT plus usual care group will also be asked to complete a Patient Satisfaction Survey at T3.

**While in-person will be the primary method for obtaining consent from participants, we recognize that not all participants are able to attend their appointments due to the effects of their illness and treatments. As such, we will also offer the option to provide consent virtually via REDCap.**

**Participant eligibility:** *Inclusion criteria*: 1) 18 years of age or older 2) Must have received a hematologic cancer diagnosis; 3) Awaiting alloBMT; 4) able to communicate in English; 5) able to access online study material (Physitrack and education e-modules). *Exclusion criteria:* 1) Not meeting the above criteria*.* **Outcomes: *Primary outcome:*** Feasibility and safety will be assessed and interpreted using quantitative and qualitative data and include *demand/uptake of the intervention, retention and adherence, and acceptability* in line with guidelines for feasibility studies. *Adverse events* that are a result of participation in the intervention will be documented. ***Secondary clinical outcomes:*** *physical function* (SF-36, 6MWT, Sit-to-stand and grip strength), *disability* (WHODAS 2.0), *nutritional status* (caloric intake, BMI, PG-SGA), *distress* (GAD-7), *QoL* (FACT-BMT, EQ5D), *healthcare utilization* (days in hospital, readmission), and *overall survival*. In addition to these patient related outcomes measures, demographic data will also be collected at baseline (only). These include: age, cancer diagnosis, gender, marital status, language, ethnicity, education, employment status, socioeconomic status, living arrangement, participation in other clinical/research studies, comfort level with English, exercise routine prior to and after cancer diagnosis and treatment as well as current exercise/activity. *Economic analysis:* compare the cost and effect between groups showing the intervention’s value for money from the payer perspective. **Analyses:** Quantitative feasibility outcomes will be summarized by descriptive statistics. Interview scripts (acceptability) will undergo inductive and deductive analyses and the constant comparative method.

For exploratory efficacy outcomes that are either continuous or categorical in nature, repeated measures analysis will be conducted by using Linear mixed models or GEE. **Sample size and timeline:** Based

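### Safety is to be compared with standard care, but the only adverse event rule covers events caused by the intervention, so the control arm yields no adverse event data

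*Protocol*

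**What the plan says.** All of the following is in the protocol; unless noted, it stands in Section 3.0, Objectives and Methods.

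- **Objective.** Objective (i) is to test the feasibility and safety of the program added to standard best practice "care compared to standard best practice cancer care alone".
- **Primary outcome.** "Feasibility and safety will be assessed and interpreted using quantitative and qualitative data". The components then named are uptake, retention and adherence, and acceptability, all of them feasibility measures. The safety provision is the next sentence: adverse events "that are a result of participation in the intervention will be documented". No other adverse event recording is described for either arm.
- **Arms.** 1:1 randomisation, 40 to usual care and 40 to the program plus usual care.
- **Other outcomes that bear on harm.** Healthcare utilization (days in hospital and readmission) and overall survival are secondary clinical outcomes, with no restriction to one arm. Objective (ii) lists "healthcare utilization, and survival" under preliminary efficacy.
- **Visits.** After baseline, assessments take place at "transplant hospital admission (T1), hospital discharge (T2), and 3-months post-discharge (T3"). They are not limited to one arm.
- **Contact.** Section 2.0, item 5, gives program participants remote check-ins at weeks 2 and 4 before admission, and at weeks 1 to 8, 10 and 12 after discharge. None is described for usual care.

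**The concern.** The objective and the collection rule do not fit together. The objective asks for a contrast with standard care. The rule counts an event only if it results from taking part in something that one arm does not receive. The control count is then zero by definition, whatever happens to those patients.

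The intervention-arm count is fragile too. Section 1.0 says that the transplant itself carries infections, drug toxicity, weight loss, graft failure, graft-versus-host disease and significant treatment-related mortality. Against that background, someone must decide that an event came from the program before it is documented. Participants and program staff know the allocation, and the protocol does not say who makes the judgement. An event made more likely by the program can be put down to the transplant and left unrecorded. Equally, a background event can be put down to the program.

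Randomisation would make this judgement unnecessary if the same events were counted in both arms. As written, the trial does not use that advantage for adverse events. The gap lies in data collection, so a statistical analysis plan cannot close it: events that were never recorded cannot be analysed later.

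**Working it through.** The protocol gives no adverse event rate and no safety-based sample size, so there is no figure of its own to reproduce. Every event rate below is an assumption. The inputs from Section 3.0 are 40 patients per arm, 1:1 allocation and α = 0.05, taken here as two-sided.

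**1. What the rule records.** Let p be the true proportion of patients with an adverse event, the same in both arms, and let a be the share of those events attributed to the program.

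- Intervention arm: recorded proportion = p × a; expected patients = 40 × p × a.
- Usual-care arm: recorded proportion = 0, because no control event can qualify.

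| Assumed p (both arms) | Assumed a | Intervention, expected of 40 | Usual care |
|---|---|---|---|
| 10% | 10% | 40 × 0.10 × 0.10 = 0.4 | 0 |
| 30% | 25% | 40 × 0.30 × 0.25 = 3.0 | 0 |
| 50% | 50% | 40 × 0.50 × 0.50 = 10.0 | 0 |

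The true difference is zero in every row. Any recorded difference comes from attribution and not from excess harm.

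**2. What the one-arm count can support.** With 0 attributed events in 40, the exact (Clopper-Pearson) upper limits are:

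- two-sided 95%: 1 − 0.025^(1/40) = 8.8%
- one-sided 95%: 1 − 0.05^(1/40) = 7.2%

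These limits reflect n = 40 and would apply to any count of 0 of 40. They show only that a clean one-arm count is weak evidence by itself.

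**3. What the same recording in both arms would give.** At a common rate p, the approximate 95% half-width for the risk difference is 1.96 × √(2p(1 − p)/40):

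- p = 10%: 0.13
- p = 30%: 0.20
- p = 50%: 0.22

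Power for 10% versus 20%, by the normal approximation (two-sided α = 0.05):

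- standard error under the null, pooled rate 15%: √(2 × 0.15 × 0.85/40) = 0.0798
- standard error under the alternative: √((0.10 × 0.90 + 0.20 × 0.80)/40) = 0.0791
- power = Φ((0.10 − 1.96 × 0.0798)/0.0791) = Φ(−0.71) ≈ 24%

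The same method gives about 45% for 30% versus 50%, and about 78% for 30% versus 60%. A descriptive comparison becomes possible, but not a well-powered test.

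**4. Contact.** The intervention arm has 2 + 8 + 2 = 12 scheduled check-ins. The topics listed for them do not include adverse events. Under the present rule the imbalance cannot bias a comparison, because there is none to bias. It matters once events are counted in both arms, since check-ins would then be a source open to one arm only.

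**The case against.** **Both arms do supply some information on harm.** A reader might infer that the control arm gives no safety data at all, or that an excess of deaths or admissions ascribed to the transplant would go unseen. The protocol does not support this. Readmission, days in hospital and overall survival are planned without restriction to one arm and do not depend on attribution. This objection stands, and it limits the point to adverse events. What those outcomes would miss are events such as falls or minor bleeds that neither cause a readmission nor affect length of stay or survival.

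**The text does not forbid wider recording.** It says that intervention-related events will be documented and does not say that others will not be. That is correct; the word only in this point is inferred from silence. Still, the protocol provides for nothing else, and a site that follows it would collect nothing else.

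**The comparison may not be meant literally.** Uptake, adherence and acceptability of a program are largely one-arm quantities. The analysis stated for the quantitative feasibility outcomes is descriptive, and no safety threshold or test is set. The comparative phrase in objective (i) may simply describe the randomised design. This is a fair reading, and it is why restating the objective is an acceptable remedy. It does not remove the mismatch in the present text. It would also go too far to call safety half of the primary outcome: the protocol gives it no weight, only one sentence after the feasibility components.

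**Recording events in both arms will not settle safety either.** This stands, as the power figures show. The gain is a comparison free of attribution, and that suits a feasibility trial.

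**Conclusion.** The point holds in this form: the comparative safety objective cannot be answered from adverse events, because the stated rule gives 0 of 40 in the control arm by definition. This follows from the wording alone and needs no assumed rate. It rests on reading the adverse event sentence as the whole of the planned recording, and no other provision appears in the protocol.

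Harm can still be compared through readmission, days in hospital and survival, which are now labelled secondary and placed under efficacy. The size of any distortion in the intervention-arm count is unknown. Under the assumed ranges (equal true rates of 10% to 50%, with 10% to 50% of events attributed), it runs from 0.4 to 10 recorded patients against none, with no true difference.

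The sentence should be changed while events can still be collected prospectively.

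**What to change.** Replace the adverse event sentence in Section 3.0 so that:

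- serious adverse events and a short pre-specified set of exercise-relevant events, chosen by the clinical team (falls, fractures, bleeding and syncope are examples), are recorded in both arms from randomisation to T3, whatever the presumed cause;
- the sources are the same in both arms: the T1, T2 and T3 visits and chart review;
- relatedness to the program is an added field and not a condition for recording;
- events found only at intervention check-ins are reported separately and kept out of the between-arm comparison;
- readmissions and deaths are also presented by arm as safety data;
- results are given as risk differences with 95% confidence intervals, described and not tested.

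If the team does not want this, objective (i) should be restated so that safety is a one-arm, descriptive objective. Either change resolves the contradiction.

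The cost is protocol wording, a short event form at visits that already exist, and chart review for the 40 control patients, for whom admissions and survival are already planned outcomes. No extra visits are needed.

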**Appendix 1: Program Description and SUNDAE Framework**

**CaRE-4-alloBMT Program Description** **
[figure not shown]
**

[figure not shown]

**SUNDAE Framework Elements in the CaRE program**

[figure not shown]

[figure not shown]

The CaRE program integrates principles of supportive communication including: fostering a therapeutic relationship, problem Defn, providing Info and support, responding to emotions & encouraging patients to take action.

The CaRE program includes proactive assessment and addresses gaps in care delivery. Further, its design focuses on reducing barriers and disparities in access to care & improving coordination, resulting in more efficient and effective supportive care.

eHealth, which is a large component of the CaRE program, can improve quality of care and access to care. Plus, it offers potential to increase the frequency and intensity of rehab

that patients are able to receive.

Within the CaRE program, engagement is viewed as a co- constructed *process* through the relationship with the alloBMT/CRS HCPs and as a *state* expressed through observable and supported behaviours.

**APPENDIX 2: Study Flow Chart and Timeline** **
[figure not shown]
**

[figure not shown]

**Leveraged funds:** The CaRE-4-alloBMT program leverages existing resources and investments (CRS and alloBMT). This includes considerable resources which have been used to develop the existing CaRE program such as emodule development (~$92,000) and development of the clinician dashboard (~$20,000) and evaluation of the CaRE model (~$50,000). These funds have come from Foundation funds, Chair funds and grants (CCO, CCS).

**In-kind funding:** In-kind support is also provided for the current project through the Butterfield Drew Chair in Cancer Survivorship Research ([name]) and the Gloria and Seymour Epstein Chair in Cell Therapy and Transplantation ([name]). This incudes the development of an alloBMT nutrition specific emodule (in development ~$4,800) and Fitbits ($4,400). In addition, both the CRS and alloBMT team have already invested considerable staff time in the development of this program and are committed to continuing the support this program through staff resources.

